# Small incision lenticule extraction (SMILE) versus laser in-situ keratomileusis (LASIK): study protocol for a randomized, non-inferiority trial

**DOI:** 10.1186/1745-6215-13-75

**Published:** 2012-05-31

**Keywords:** Refractive surgery, Laser in situ keratomileusis, Small incision lenticule extraction

## Abstract

**Background:**

Small incision lenticule extraction or SMILE is a novel form of ‘flapless’ corneal refractive surgery that was adapted from refractive lenticule extraction (ReLEx). SMILE uses only one femtosecond laser to complete the refractive surgery, potentially reducing surgical time, side effects, and cost. If successful, SMILE could potentially replace the current, widely practiced laser in-situ keratomileusis or LASIK. The aim of this study is to evaluate whether SMILE is non-inferior to LASIK in terms of refractive outcomes at 3 months post-operatively.

**Methods/Design:**

Single tertiary center, parallel group, single-masked, paired-eye design, non-inferiority, randomized controlled trial. Participants who are eligible for LASIK will be enrolled for study after informed consent. Each participant will be randomized to receive SMILE and LASIK in each eye. Our primary hypothesis (stated as null) in this non-inferiority trial would be that SMILE differs from LASIK in adults (>21 years old) with myopia (> −3.00 diopter (D)) at a tertiary eye center in terms of refractive predictability at 3 months post-operatively. Our secondary hypothesis (stated as null) in this non-inferiority trial would be that SMILE differs from LASIK in adults (>21 years old) with myopia (> −3.00 D) at a tertiary eye center in terms of other refractive outcomes (efficacy, safety, higher-order aberrations) at 3 months post-operatively. Our primary outcome is refractive predictability, which is one of several standard refractive outcomes, defined as the proportion of eyes achieving a postoperative spherical equivalent (SE) within ±0.50 D of the intended target. Randomization will be performed using random allocation sequence generated by a computer with no blocks or restrictions, and implemented by concealing the number-coded surgery within sealed envelopes until just before the procedure. In this single-masked trial, subjects and their caregivers will be masked to the assigned treatment in each eye.

**Discussion:**

This novel trial will provide information on whether SMILE has comparable, if not superior, refractive outcomes compared to the established LASIK for myopia, thus providing evidence for translation into clinical practice.

**Trial registration:**

Clinicaltrials.gov NCT01216475.

## Background

Laser in-situ keratomileusis (LASIK) is the current laser refractive procedure of choice to treat myopia. The advantages of LASIK include early postoperative improvement and stabilization of visual acuity, minimal postoperative patient discomfort, and the possibility of enhancement in the future [1]. However, side effects such as dry eyes, reduced vision in low lighting conditions, and visual distortions such as glare and haloes can still occur in up to 1% to 2% of cases; while flap-related complications, inflammation, or infection, though rare, can have serious consequences [2,3].

Femtosecond lasers have been widely used in LASIK to fashion a corneal flap, which is followed by corneal ablation using a separate excimer laser [4]. The advantages of femotosecond or ‘bladeless’ LASIK over microkeratome LASIK flaps are reduced postoperative dry-eye symptoms, reduced likelihood of flap dislocation, and reduced incidence of buttonholes or free caps [2,3]. Recently, refractive lenticule extraction (ReLEx) has been introduced as a single laser refractive procedure without the use of an excimer laser [5-8]. Small incision lenticule extraction (SMILE) is a variation of ReLEx that requires no retractable flap, thus reducing surgical time, reduced patient inconvenience from moving from one laser to another, and, potentially, more accurate ablation [8].

A review of current literature reveals that there are few studies available to validate the outcome of ReLEx or SMILE, which has obtained CE Mark approval in 2009 but yet to be approved by the United States FDA [5-8]. Initial clinical results have been promising, which found that postoperative refractive outcomes after ReLEx were comparable to LASIK with few complications [9,10]. However, there are currently no randomized controlled trials comparing both surgical procedures. We have also conducted preliminary clinical and experimental studies with promising results and confirmed the safety and efficacy of ReLEx [11].

Non-inferiority trials are used to compare standard treatment with a new treatment that is expected to have some advantages such as greater predictability, less side effects, or greater improvement in quality of life [12,13]. LASIK, which is the current gold standard for corneal refractive surgery, already produces good visual outcomes with refractive predictability. As we do not expect to see a great improvement to the results from the already established LASIK, we aim to demonstrate that SMILE is just as good in terms of visual outcome in this randomized non-inferiority trial.

## Methods/Design

### Study objective and hypotheses

In this study we aim to demonstrate that the refractive predictability of SMILE is not inferior to the established procedure (LASIK) to treat myopia. Refractive predictability is one of several standard refractive outcomes, defined as the proportion (number) of eyes achieving a postoperative spherical equivalent (SE) within ±0.50 diopter (D) of the intended target. Our primary hypothesis (stated as null) in this non-inferiority trial would be that SMILE differs from LASIK in adults (>21 years old) with myopia (> −3.00 D) at a tertiary eye center in terms of refractive predictability at 3 months postoperatively. Our secondary hypothesis (stated as null) in this non-inferiority trial would be that SMILE differs from LASIK in adults (>21 years old) with myopia (> −3.00 D) at a tertiary eye center in terms of other refractive outcomes (efficacy, safety, higher-order aberrations) at 3 months postoperatively.

### Trial design

This trial is a single tertiary center, parallel group, single-masked, paired-eye design, non-inferiority, randomized controlled trial. We will use a paired-eye study design, with subjects randomly assigned to undergo one procedure in each eye (SMILE in one eye, LASIK in the other eye). All procedures will be performed in the SNEC Refractive Center by the same fully qualified refractive surgeons, who are co-investigators in this study. Each surgeon has performed more than 30 similar surgeries and 20 cases of SMILE to ensure that each surgeon is adept at performing this procedure. After randomization and random allocation to treatment group, each subject will undergo either SMILE or LASIK in one eye, followed by LASIK or SMILE in the fellow eye on the same day (either the left or right eye will be randomized to decide which eye is operated on first). We have obtained ethics approval from our Institutional Review Board (CIRB Ref No: 2011/109/A) and this trial has been registered (Clinical Trials Registration NCT01216475).

### Participants and recruitment

All participants with bilateral myopia will be recruited at the Singapore National Eye Center (SNEC) with the inclusion and exclusion criteria detailed in Table 1. All subjects will be recruited and provide written informed consent that explains the details of the trial, interventions, and study protocol in accordance with the principles of the Declaration of Helsinki.

**Table 1 T1:** Inclusion and exclusion criteria for trial participants

**Inclusion criteria**	**Exclusion criteria**
I. 21 years of age or older	I. Progressive or unstable myopia and/or astigmatism
II. Cycloplegic spherical equivalent of >−3.00 D in BOTH eyes	II. Clinical or corneal topographic evidence of keratoconus
III. Refractive cylinder −2.00 D or less in BOTH eyes and anisometropia of <1D comparing BOTH eyes	III. Residual, recurrent or active ocular disease such as uveitis, severe dry eyes, severe allergic eye disease, glaucoma, visually significant cataract, and retinal disease
IV. Best spectacle corrected visual acuity (BSCVA) of 6/12 or better in BOTH eyes	IV. Previous corneal surgery or trauma within the corneal flap zone
V. Spherical or cylindrical error has progressed at −0.50 D or less per year from date of baseline measurement in BOTH eyes	V. Patent corneal vascularization within 1 mm of the corneal flap zone
VI. Contact lens wearers must have removed contact lenses at least 2 weeks before the baseline measurement	VI. Taking systemic medications likely to affect wound healing, such as corticosteroids and antimetabolites. Systemically immunocompromised or systemic disease likely to affect wound healing, such as diabetes, connective tissue disease, and severe atopy; pregnant or nursing
VII. No evidence of irregular astigmatism on corneal topography in BOTH eyes	

### Surgical interventions

#### SMILE procedure

Each SMILE procedure will be performed using an established, described technique [7]. After application of topical anesthesia, standard sterile draping, and insertion of the speculum, the patient’s eye will be centered and docked with the curved interface cone before application of suction fixation. The laser will then be activated for photo-dissection in the following sequence: first the posterior surface of the refractive lenticule (spiral in), then the lenticule border is created. The anterior surface of the refractive lenticule (spiral out) is then formed which extended beyond the posterior lenticule diameter by 0.5 mm to form the anterior flap and is followed by a rim cut. We will use the following FS laser parameters: 120 μm flap thickness, 7.5 mm flap diameter, 6.5 mm optical zone of lenticule, 145 nj of power with side cut angles at 90°. A superior hinge, 50° in cordal length, will be made in all cases. The spot distance and tracking spacing are 3/3 μm for the lenticule, 2.5/2.5 μm for the lenticule side cut, 3/3 μm for the flap, and 2/2 μm for the flap side cut. After the suction is released, a Siebel spatula (Rhein Medical, Heidelberg, Germany) is inserted under the flap near the hinge before the flap is separated and reflected. The edge of the refractive lenticule is separated from the stromal bed with a sinsky hook and the posterior border of the lenticule gently separated with the Siebel spatula. The lenticule is then grasped with non-toothed serrated forceps through the small incision.

#### LASIK procedure

Each LASIK procedure will be performed using a standard, established technique. Under topical anesthesia and standard draping, a lid speculum is used to retract the eyelids, and polyvinyl acetate surgical spears (Ivalon, New London, CT) to dry the conjunctival fornices. A superiorly hinged 120/140 μm thick flap will be created using the Visumax femtosecond laser (Carl Zeiss). Excimer laser ablation is then performed using Wavelight Allegretto WAVE Eye-Q 400 Hz excimer laser (Wavelight GmbH, Alcon, Fort Worth, TX, USA). After ablation, the flap will be carefully repositioned, and postoperative medications are commenced.

### Outcomes

We plan to use standard primary and secondary outcomes measures at 3 months postoperatively, which are reported in any assessment refractive surgical technique and standard outcomes in refractive studies. Measurements and outcomes are based on visual acuity (VA) and refraction that are performed by trained refractive optometrists and are repeatedly tested to ensure accuracy and reproducibility. Our primary outcome measure is refractive predictability, which is defined as the proportion number of eyes achieving a postoperative spherical equivalent (SE) within ±0.50 D of the intended target.

Secondary outcome measures include: (1) Efficacy: defined as the proportion number of eyes achieving a unaided visual acuity (UAVA) of 20/20 or better postoperatively; (2) Safety: defined as the proportion number of eyes that lost or gained one or more lines of postoperative best-corrected visual acuity (BCVA) relative to the preoperative BCVA; (3) Higher-order aberrations (HOAs): measured using the Bausch and Lomb Technolas Zywave aberrometer with Zywave software version 4.45 (ZYOPTIX Diagnostic Workstation, Bausch & Lomb); (4) Contrast sensitivity: tested using the Vision Contrast Test System (VCTS) chart (VCTS 6500 contrast sensitivity chart) in six spatial frequencies.

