### Statistical analyses

Demographic and baseline information will be described, and eye-specific characteristics will be described for each treatment. To study the non-inferiority of SMILE to LASIK, a 90% confidence interval of the difference in predictability between the two treatments (LASIK minus SMILE) will be constructed by a method using score intervals with continuity correction (method #10 in Newcombe RG, 1998) [15]. If the upper limit of the 90% confidence interval does not exceed the pre-defined non-inferiority margin of 5%, non-inferiority is confirmed. Similarly, for each of the two secondary outcomes, efficacy, and safety, a 90% confidence interval of the difference between the two treatments using the above-mentioned method will be constructed and then compared with a non-inferiority margin of 5%. Assuming the other secondary outcome, HOA, follows a normal distribution, a 90% confidence interval of the difference between the two treatments will be constructed through a paired *t*-test, and then compared with a non-inferiority margin of 10%. We would not be performing any interim analyses due to the short duration of follow-up for each outcome measure.

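### The safety endpoint puts eyes that lost lines and eyes that gained lines into one proportion, so its 5% non-inferiority test has no worse direction and cannot show that SMILE is no less safe than LASIK

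*Protocol article*

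**What the plan says.** In the protocol article, Outcomes lists among the secondary measures "Safety: defined as the proportion number of eyes that lost or gained one or more lines of postoperative best-corrected visual acuity (BCVA". The change is counted from the value before surgery, and the measure is described as one proportion.

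The primary outcome is "the proportion number of eyes achieving a postoperative spherical equivalent (SE) within ±0.50 D of the intended target", and the first secondary outcome is "Efficacy: defined as the proportion number of eyes achieving a unaided visual acuity (UAVA) of 20/20 or better postoperatively". For both, a higher proportion is better.

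Statistical analyses gives one complete decision rule, for the primary outcome. The interval is for the "difference in predictability between the two treatments (LASIK minus SMILE) will be constructed", and "If the upper limit of the 90% confidence interval does not exceed the pre-defined non-inferiority margin of 5%, non-inferiority is confirmed".

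The next sentence turns to the secondary outcomes: "Similarly, for each of the two secondary outcomes, efficacy, and safety, a 90% confidence interval of the difference between the two treatments" is to be built, "using the above-mentioned method will be constructed and then compared with a non-inferiority margin of 5" per cent. It does not restate which treatment is subtracted from which, or which limit is read. Losses and gains are not separated anywhere in that section.

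**The concern.** A non-inferiority test needs an endpoint for which one direction is worse. The proportion of eyes whose corrected acuity changed by a line in either direction has no such direction. A margin on it limits how far the procedures differ in how often acuity changes, and says nothing about how often it deteriorates.

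The direction adds to this. The stated rule suits outcomes where a high proportion is good. The wording that links it to safety is the word *similarly* and a reference back to the method, with no reversal. For an event that includes harm, more affected SMILE eyes make LASIK minus SMILE more negative and pull the upper limit further below the margin.

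At stake is the only between-procedure safety test that the article describes. The Adverse events section covers monitoring and reporting, not a comparison, and the Discussion presents SMILE as a possible successor to LASIK.

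**Working it through.** **Inputs.** From the protocol: 67 pairs (Sample size); a 90% interval by Newcombe's paired score method 10 with continuity correction, and a 5% margin (Statistical analyses). The protocol gives no rate of lost or gained lines and no safety calculation, so there is no plan figure to reproduce. All rates below are assumptions. The correlation between a subject's two eyes is also not given, so it is varied.

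**Step 1. The pooled proportion hides opposite outcomes.** Pooled rate = lost + gained.

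| | Lost | Gained | Pooled |
|---|---|---|---|
| LASIK | 5% | 15% | 20% |
| SMILE | 15% | 5% | 20% |

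The true pooled difference is 20% − 20% = 0, although losses are three times as frequent with SMILE. Exact enumeration gives the probability that the upper limit of LASIK − SMILE is at most 5%: 0.177, 0.222 and 0.337 when the proportion of pairs with an event in one given eye only is 0.16 (independent eyes), 0.10 and 0.05. With equal marginal rates, reversing the sign gives the same probabilities. They are what two equal 20% rates yield at this sample size, whatever the mix of losses and gains.

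**Step 2. The stated direction applied literally to the pooled endpoint.** Take LASIK 5% lost + 15% gained = 20%, and SMILE 15% lost + 15% gained = 30%. The whole increase is loss. With independent eyes (both eyes affected: 0.20 × 0.30 = 0.06), the upper limit of LASIK − SMILE is at most 5% in about 64% of trials. The range is about 55% with no overlap between eyes to 100% with maximal overlap.

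**Step 3. The same direction applied to losses only.** This is not the endpoint the protocol defines. It shows what happens if losses are split off and the direction is left alone.

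| True loss, LASIK / SMILE | Upper limit of LASIK − SMILE ≤ 5% | Upper limit of SMILE − LASIK ≤ 5% |
|---|---|---|
| 5% / 15%, independent eyes | 0.90 | 0.004 |
| 5% / 15%, LASIK-only pairs 0.02 | 0.96 | 0.002 |
| 15% / 5%, independent eyes | 0.004 | 0.90 |

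The unreversed rule passes the procedure with more losses and fails the one with fewer.

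**Step 4. One data set by hand.** Losses in 3/67 LASIK and 10/67 SMILE eyes, none in both eyes of a pair.

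- Difference: 3/67 − 10/67 = 0.0448 − 0.1493 = −0.1045.
- 90% Wilson limits: LASIK 0.0180 to 0.1069; SMILE 0.0914 to 0.2344.
- Correlation term: φ = (0×54 − 3×10)/√(3×64×10×57) = −0.0907. It is negative, so the continuity correction leaves it unchanged.
- Upper limit: −0.1045 + √(0.0579² + 0.0621² + 2×0.0907×0.0579×0.0621) = −0.1045 + 0.0887 = −0.016.
- Lower limit: −0.1045 − √(0.0267² + 0.0851² + 2×0.0907×0.0267×0.0851) = −0.1045 − 0.0915 = −0.196.

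The interval, −19.6% to −1.6%, lies wholly on the side of more loss with SMILE. Its upper limit is below 5%, so an unreversed rule would confirm non-inferiority.

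**The case against.** A reader might infer that the protocol fixes the wrong direction for safety and so gives a harmful SMILE a 90–96% chance of passing. The text does not support that.

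- LASIK minus SMILE and the upper-limit rule are attached to predictability. The safety sentence speaks only of a difference between treatments, and the reference back to the method may mean just the interval formula. The sentence on higher-order aberrations also gives no direction, although the Discussion presents a reduction there as the benefit. The direction for safety is therefore unstated, and the carry-over is inferred.
- The 90–96% belongs to a loss-only endpoint that the protocol does not define. Pooled and loss-only are alternative readings, so the two defects do not add up at full strength.
- Nor does the concern run both ways. A SMILE arm with many gains could not be misread as unsafe under the carried-over direction, because extra SMILE events help it pass.

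The phrase about lost or gained lines may also be shorthand for two separately reported proportions, and anyone tabulating acuity change would see losses and gains apart. Safety is one of four secondary outcomes, and it drives neither the sample size nor any interim decision.

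These arguments limit the size and certainty of the direction problem. They do not remove the pooling. The article describes one proportion, one interval and one margin, and does not say that two proportions are meant. If two were meant, they would need opposite directions, and at most one is given. Nor is this a detail left to an analysis plan: the definition and the margin are stated, and an analysis plan would have to rewrite them.

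**Conclusion.** The point holds in this form. As written, the safety endpoint has no worse direction, and a 5% non-inferiority test on it cannot show that SMILE is no less safe. This rests on the text alone; the 20% against 20% example only illustrates it.

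The direction problem is conditional. If the predictability rule is carried over unreversed, it becomes easier to pass as SMILE events increase: about 64% for pooled 20% against 30% with independent eyes. All event rates and between-eye correlations are assumptions.

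The endpoint is secondary, so this should be fixed before analysis. It does not threaten the primary comparison.

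**What to change.** In Outcomes, define safety as the proportion of eyes losing one or more lines of corrected acuity relative to the preoperative value, and report gains separately and descriptively. In Statistical analyses, state that safety is non-inferior if the upper limit of the 90% interval for SMILE minus LASIK in the proportion losing lines does not exceed the 5% margin already set there.

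The cost is two sentences. Acuity is already collected, so no new data are needed. One consequence should be accepted openly: if both procedures truly lose a line in 5% of eyes, with independent eyes, the corrected test passes in only about 33% of trials of 67 pairs. Failure to confirm non-inferiority on safety should then not be read as evidence of harm.

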### Sample size

As this is a paired design, non-inferiority trial with a binary outcome, we calculate the required sample size using the maximum likelihood method for large sample proposed by Nam (1997) [14]. A review of current literature reveal that the reported refractive predictabilities in LASIK and SMILE range from 78.2% to 96.7% [1,14,15] and from 90.0% to 95.6%, [5-8], respectively. The results from our own audit department estimate our refractive predictability at 82% for LASIK (2011, unpublished). We therefore assumed the refractive predictabilities in LASIK and SMILE in this study are 82% and 92%, respectively. Thus, a sample of 67 subjects (134 eyes) will be sufficient to confirm non-inferiority with a power of ≥80% and at a 5% significance level using a 10% non-inferiority margin, which is the clinically significant difference from our preliminary data. To account for a lost to follow-up rate of 5%, 70 subjects will be recruited.

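### The primary non-inferiority margin is 10% in the sample-size section and 5% in the success rule, and 67 subjects at 80% power fits 5%, not 10%

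*Protocol article*

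**What the plan says.** The Sample size section uses a method for paired binary data: "we calculate the required sample size using the maximum likelihood method for large sample proposed by Nam (1997"). Its assumed rates are explicit: "We therefore assumed the refractive predictabilities in LASIK and SMILE in this study are 82% and 92%, respectively". It concludes that "a sample of 67 subjects (134 eyes) will be sufficient to confirm non-inferiority with a power of ≥80"%, "at a 5% significance level using a 10% non-inferiority margin, which is the clinically significant difference from our preliminary data". The section does not say whether the 5% level is one-sided or two-sided, and it gives no correlation or discordance between the two eyes of a subject.

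The Statistical analyses section sets the test of the same outcome: "a 90% confidence interval of the difference in predictability between the two treatments (LASIK minus SMILE) will be constructed". The decision rule is: "If the upper limit of the 90% confidence interval does not exceed the pre-defined non-inferiority margin of 5%, non-inferiority is confirmed". The same section uses 5% again for efficacy and safety. Its only 10% margin is for higher-order aberrations, a continuous secondary outcome.

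**The concern.** The margin is the one number that decides whether this trial succeeds. Both statements are current text, both concern predictability at 3 months, and both present the margin as settled: one calls 10% the clinically significant difference, the other calls 5% pre-defined. This is a conflict in what the document states, so a fuller analysis plan would not remove it.

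Two things are at stake. First, a reader cannot tell which loss of predictability the trial is designed to exclude, and the only reason offered for any margin is attached to the one that the decision rule does not use. Second, the power statement is tied to a margin other than the one that will be applied, so it does not describe the planned test.

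**Working it through.** **Inputs from the protocol.** LASIK 82%, SMILE 92%, so the true difference is d = 0.10 in favour of SMILE. Power is at least 80% and the significance level 5%. One procedure is done in each eye of a subject. The decision uses the upper limit of a 90% interval, which amounts to a one-sided 5% test.

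**Assumption.** Discordance is not stated. Let b be the probability that only the LASIK eye succeeds and c = b + 0.10 the probability that only the SMILE eye does. Independent eyes give b = 0.82 × 0.08 = 0.0656 and c = 0.1656. The feasible range of b is 0 to 0.08, because SMILE fails in only 8%.

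**Formula (Nam, restricted maximum likelihood), margin δ.**

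n = [z(1−α)·√V0 + z(power)·√V1]² / (d + δ)²

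- V1 = b + c − d² = 0.0656 + 0.1656 − 0.01 = 0.2212, so √V1 = 0.4703.
- V0 = 2q + δ − δ², where q is the restricted estimate of the SMILE-only probability at the null. It solves c/q + b/(q+δ) = 2(1−b−c)/(1−2q−δ).

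**Reproducing 67 (one-sided 5%, 80% power, independent eyes).**

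- δ = 0.05: q = 0.1018, V0 = 0.2510, √V0 = 0.5010. n = [(1.645 × 0.5010 + 0.842 × 0.4703)/0.15]² = 66.1, i.e. **67**, the stated figure.
- δ = 0.10: q = 0.0918, V0 = 0.2736, √V0 = 0.5230. n = [(1.645 × 0.5230 + 0.842 × 0.4703)/0.20]² = 39.4, i.e. **40**.

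**Power at 67** = Φ{[√67·(d+δ) − 1.645·√V0]/√V1}.

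- δ = 0.05: (1.228 − 0.824)/0.4703 = 0.86, power 80.5%.
- δ = 0.10: (1.637 − 0.860)/0.4703 = 1.65, power 95.1%.

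**Over feasible discordance (one-sided 5%).**

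| b | n for 80%, 5-point | n for 80%, 10-point | Power at 67, 5-point | Power at 67, 10-point |
|---|---|---|---|---|
| 0 | 34 | 23 | 98% | 99.9% |
| 0.0656 (independent) | 67 | 40 | 80.5% | 95.1% |
| 0.08 (maximum) | 74 | 44 | 77% | 93% |

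At one-sided 2.5% and 80% power, a 10-point margin needs 51 with independent eyes (30 to 56 over the range). So no 10-point design at an 80% target reaches 67.

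**Under the planned interval.** At n = 67 with independent eyes, the hybrid score interval with the continuity correction on the correlation term gives power of 82.7% (5%) and 96.4% (10%). If the single-proportion limits are corrected as well, it gives about 77% and 95%.

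**How often the two margins disagree.** These figures use the first form of that interval, n = 67 and independent eyes:

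- 82% versus 92%: 96.4 − 82.7 = 13.7% of trials have an upper limit between 5% and 10%.
- Both procedures at 82%: about 26%.
- SMILE truly 5 points worse (LASIK 87%, SMILE 82%): non-inferiority is declared in about 5% of trials with the 5% margin and about 19% with the 10% margin.

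These depend strongly on discordance. The first runs from near 0 to 16%. The second is lowest as discordance vanishes and exceeds 40% at low to moderate values. In the third, the 10%-margin figure runs from 18% to 38%. The last two scenarios are illustrations and are not in the protocol.

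**The case against.** Four points can be made for the plan.

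1. **The power claim survives.** The text promises at least 80%, and with independent eyes 67 delivers that under either margin. This stands. A reader might infer from the clash that the trial is underpowered; the figures do not show it. Power falls slightly below 80% under the 5% margin only if discordance is near its maximum or the heavier continuity correction is used, and the protocol fixes neither.

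2. **67 is not unique to a 5% margin.** The match needs independent eyes, which the protocol does not state; at 5% the required number runs from 34 to 74. A 10% margin with one-sided 2.5% and 90% power also gives 67: [(1.960 × 0.5230 + 1.282 × 0.4703)/0.20]² ≈ 66.3. This stands as a limit on the inference. A reader might say that 67 can come only from 5%, which is too strong. But the rival reading needs a power target that the text does not state and a test that the 90% interval does not perform.

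3. **Only one section contains a decision rule.** Read literally, the operative margin is the stricter 5%, and the 10% is only a sizing statement. This reduces the ambiguity without removing it, because the sizing section calls its figure the margin and gives the only clinical reason for one.

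4. **A back-calculation cannot show which margin is clinically right.** This stands. It shows which value probably entered the calculation, so the justification must come from the sponsor.

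**Conclusion.** The contradiction is explicit and needs no assumption: 10% for sizing and 5% for the decision, on the same primary outcome. It must be resolved because it sets the success threshold.

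That 10% does not fit 67 is nearly as firm. At one-sided 5% and 80% power with the named method and stated rates, 10% needs between 23 and 44 subjects whatever the discordance. That 10% is a slip for 5% is probable but not proven: 5% reproduces 67 if the eyes are independent, and it is the margin in the decision rule, but the protocol does not say so.

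The defect lies in the margin attached to the power statement. Power under the 5% margin at 67 is about 80.5% with independent eyes and 77% to 98% over feasible discordance, so a conclusion that the trial is too small would go beyond the document.

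**What to change.** State one primary margin, give its justification, and use it in both sections. Five points is the choice consistent with the decision rule and with 67.

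The sample-size sentence would then say that 67 evaluable subjects give about 80% power at one-sided 5% with a 5-point margin, assuming 82% for LASIK, 92% for SMILE and independent outcomes in the two eyes. The statement that 10% is the margin and the clinically significant difference should be corrected or removed, and a reason given for 5 points.

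If the sponsor keeps 10% instead, the decision rule in Statistical analyses must be changed before unblinding and the power restated as about 95% with independent eyes.

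Either way the cost is a few sentences. The 5-point wording needs no change to the target of 67 under independence. Guarding 80% power against maximum discordance would need 74 evaluable subjects, which is a choice for the sponsor and not something this correction requires.
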